### D.5.3. Missing Data Analysis

We anticipate a low rate of missing data for the primary outcome since our CHICA system showed only 1.3% error rate due to omission of a data field. However, we anticipate a possible dropout rate of 10% for which we have adjusted the sample size. It is very unlikely that dropout will depend on the unobserved outcome. Even if MNAR is true for certain subjects; given the low percentage of missing values, we think the bias induced is negligible. Under circumstances where compromise of power due to missing values is of concern, we will use a multiple imputation procedure to make use of all relevant observed data under the assumption that the data are Missing At Random. The SAS procedure MI and MIANALYZE will be used to implement the procedure.

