#### D.3.4 Patient Recruitment and Consent

The same four clinics utilized in aim 2 of the study will be utilized for aim 3 of the study. The same two clinics that served as the intervention group in aim 2 will once again serve as the intervention group for this portion of the study. These two clinics will have the ASD care and management module as part of the CHICA system. The two control clinics will have the CHICA system but will NOT have the ASD care and management module.

For this portion of the study, consent will be obtained from those patients who are newly diagnosed with ASD so that we may collect additional evaluation and assessment data beyond that which is normally documented during standard care practices. Children and their parents will be recruited and consented through the Pediatric Research Network (PResNet). PResNet is a pediatric practice based research network located at the Indiana University School of Medicine (See full description in Resources section of the proposal). PResNet was established in 2006 as an offshoot of ResNet, the very successful practice-based research network of the Indiana University Medical Group. Since 2000, ResNet has been involved in more than 40 studies supported by over \$15 million in extramural grants. In these studies, ResNet has recruited more than 7,000 patients, approximately 68% of those patients contacted (a remarkable figure, considering that two-thirds of those approached were African-American or Hispanic). In 2006, PResNet was established to facilitate pediatric specific primary care research efforts. While it does not have as long of a track record of recruiting patients as ResNet, it follows the same processes and procedures and therefore has encountered the same level of success at patient recruitment. PResNet has been involved with 8 studies in the IUMG clinics and has recruited more than 2200 patients, approximately 84% of those patients contacted. With the inclusion of the private practices, PResNet has recruited over 5000 patients, approximately 85% of those patients contacted.

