### **D.4 Sample Size (Aims 2 and 3)**

#### D.4.1. Sample Size Calculation for Aim 2

The primary outcome of interest for aim 2 is the proportion of children at the 18 or 24-month visits that will be screened for ASD using the M-CHAT in the intervention group and any ASD specific screening tool in the control group. Dosreis and colleagues found that while 82% of pediatricians reported screening for general developmental delays, only 8% screened for ASD. Though we do not anticipate much variability in this rate at our study clinics, we will use four different rates, 6%, 8%, 10% and 12%, at baseline to estimate intra-clinic correlation. This translates to an intra-class correlation coefficient 0.0041. However, for a conservative estimation of sample size, we will use intra-class correlation 0.0082, twice that of the correlation we estimated.

To be conservative, we will assume 10% of the children are screened for ASD under standard practice in our clinic sites. Based on pilot data involving a different universal screening tool in the pediatric population (i.e., the Ages and Stages Questionnaire), we expect at least 50% of the children at the 18 or 24-month visits will be screened in the intervention clinics. However, we will use a more conservative estimate, that is, 40% of the children will be screened using the M-CHAT.

Using a chi-square test and setting alpha at 0.05, the probability of detecting a statistically significant difference in the proportion of children screened at the 18 or 24-month visits between the intervention and the control group is 90% with an effective sample size of 49 per group. Hence, the total effective sample size ( $n^*$ ) is 98. The unit of randomization is the practice or clinic, but the unit of analysis is the individual patients. Since patients are nested within practice, responses from the patients within practice are likely to be correlated. This intra-cluster correlation must be taken into account in the calculation of sample size and in the analyses. We computed the number of patients per clinic,  $m$ , required for the study, using the following equation:

$$m = \frac{1 - \rho}{\frac{k}{n^*} - \rho}$$

where  $\rho$  = intra-practice correlation,  $k$  = number of clinics,  $mk$  = total sample size,  $n^*$  = total effective sample size =  $mk/DE$ , and  $DE$  = design effect =  $1 + \rho(m-1)$ 

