Using 4 clinics and assuming intra-class correlation of 0.0082, we need to recruit 31 children per clinic. We anticipate that drop-out is not a major problem and unlikely to be more than 10% for the primary outcome. We will account for this factor by oversampling patients by 10%. According to our previous experience and data from the four clinics included in this study, at least 1000 patients present to these four clinic sites for 18 or 24-month visits each year, leading to 3000 patients if the study runs for 3 years.

#### D.4.1. Sample Size Calculation for Aim 3

For aim 3, children between the ages of 18 months through 5 years with newly diagnosed ASD will be included as potential participants. The primary outcome of interest for this aim is the number of activities/involvements (listed in Figure 9) that a child diagnosed with an ASD is receiving. Although better outcomes are expected in the intervention group, no preliminary data are available to support this hypothesis. Hence, the primary purpose of this study is to generate preliminary data on this outcome in order to design a large scale study. Even though the screening rate could be as low as 8% in the intervention group and 40% in the intervention group, the vast majority of children should still receive a diagnosis of ASD by age 5 even without standardized screening at the 18 or 24-month visits. It is likely that we will have at least 80% of the children with a diagnosis of ASD receiving care for that diagnosis by age 5. Though we do not know how many children with newly diagnosed ASD will be available in each of the four clinics, we anticipate more than 20 children in each of the two treatment groups assuming a prevalence of 1 in 150, successful identification of 80% of children with diagnosis ASD, and recruiting about 4000 per group. In 2007, the four study clinics saw 8,528 patients between ages of 0 and 3 years and 3,065 patients between the ages of 4 and 5. Hence, we do not anticipate any problem in having 4000 children per group for this study. We base the sample size justification on estimation and not hypothesis testing. A sample size of 20 per group can be considered adequate for a pilot study given that a sample size as low as 12 in each group provides adequate power for precision in estimating the difference between means in clinical trials in the sense that the gains in precision are less pronounced as sample size exceeds 12.

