### **D.5 Data Analysis (Aims 2 and 3)**

For each of the two aims, baseline clinical and demographic data will be compared between the intervention and the control groups. Categorical variables will be examined using chi-square tests and continuous measures with Student's t-tests. The statistical analysis of the data will be performed using the SAS.

#### D.5.1. Data Analysis for Aim 2

The primary variable for aim 2 is whether a child at the 18 or 24-month visits was screened for ASD using the M-CHAT in the intervention group and any ASD specific screening tool in the control group. For this dichotomous outcome, we will use a non-linear mixed-effects model and will adjust for potential confounders (fixed effects) and clinic effects (random effects). To be specific, if  $Y_{ik}$  is a binary variable indicating whether the  $k^{\text{th}}$  patient in the  $i^{\text{th}}$  clinic was screened, we have

$$\log it(Y_{ik} = 1) = \alpha_i + \mathbf{X}_{ik}\boldsymbol{\beta}, \text{ where } \alpha_i \sim N(0, \varepsilon^2).$$

The random component  $\alpha_i$  correlates outcomes of patients cared by the same clinic. Physicians would not be considered as a nesting factor since the same patients at different visits may not be seen by the same physician. The vector  $\mathbf{X}_{ik}$  represents fixed covariates and  $\boldsymbol{\beta}$  represents the corresponding coefficients. The fixed covariates will include critical covariates such as treatment group, gender, and other patient and clinic level characteristics. We will also examine potential interaction terms among the covariates, particularly interactions between treatment arm and other covariates. If there is a significant treatment difference, we will report the 95% confidence interval of the treatment difference after adjusting for all confounding factors. The model will be fitted by the SAS procedure NLMIXED.

All secondary dichotomous outcomes, for example, whether a child under the age of 5 undergoes surveillance for ASDs, whether ASD surveillance led to diagnosis of ASD with an ASD specific screening tool and whether a child was referred for comprehensive ASD evaluation will also be analyzed using the same model as described above.

### D.5.2. Data Analysis for Aim 3

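### Aim 3's figure of more than 20 children per group counts diagnosed children with no allowance for refusal or dropout; at the plan's own 84% recruitment rate it is about 18 enrolled

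*Protocol*

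**What the plan says.** **Aim 3 projection (Protocol D.4.1, Sample Size Calculation for Aim 3).** The plan states that "we anticipate more than 20 children in each of the two treatment groups". It assumes a prevalence of 1 in 150, identification of 80% of affected children, and about 4000 children per group. It then calls 20 per group adequate for a pilot, on the argument that precision gains flatten above 12 per group. The 4000 is supported by the 2007 patient counts of the four clinics: 8,528 aged 0 to 3 and 3,065 aged 4 to 5.

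**What Aim 3 asks of families (D.3.4, Patient Recruitment and Consent; D.3.4, Data Collection).** Parents of newly diagnosed children are telephoned and asked for individual consent. Assessments run from baseline to 12 months after diagnosis. On past performance in the clinics of this practice group, the pediatric network "has recruited more than 2200 patients, approximately 84% of those patients contacted". Its parent network reports 68%.

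**Where a dropout allowance appears.** In D.4.1 for Aim 2, dropout is called "unlikely to be more than 10% for the primary outcome", and the Aim 2 sample is increased by 10%. D.5.3, which sits under a heading naming Aims 2 and 3, then says "we anticipate a possible dropout rate of 10% for which we have adjusted the sample size".

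**The concern.** Aim 2's primary outcome is read at the 18- or 24-month visit, with a waiver of consent requested, so little can be lost. Aim 3 is the aim in which families can decline and can leave, and its projection has no factor for either. The number of diagnosed children has been carried straight into the number of study participants.

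Aim 3 is justified on estimation, to supply data for designing a larger study. The expected number per group is therefore the main quantity that its sample-size paragraph has to get right. A reader of D.5.3 would also suppose that losses had been allowed for in both aims.

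**Working it through.** **Inputs.** From D.4.1 (Aim 3): 4000 per group, prevalence 1/150, identification 0.80. From D.3.4 (Recruitment): 0.84 of those contacted for the pediatric network in these practices, 0.85 with private practices included, 0.68 for the parent network. From D.4.1 (Aim 2) and D.5.3: 10% dropout. The plan gives no dropout rate for Aim 3, so using 10% there is an assumption.

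**1. The plan's figure.** 4000 × (1/150) × 0.80 = 21.3 per group. This reproduces the stated figure of more than 20, and only with no losses.

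**2. With losses.** Expected number = 21.33 × recruitment × retention.

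| Recruitment | Enrolled per group | With 12-month data, if 10% drop out |
|---|---|---|
| 1.00 | 21.3 | 19.2 |
| 0.85 | 18.1 | 16.3 |
| 0.84 | 17.9 | 16.1 |
| 0.68 | 14.5 | 13.1 |

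Either factor alone takes the number below 20. The recruitment rates apply to families contacted, so the table assumes that every diagnosed child's family is reached. The requirement for an English-speaking parent available by telephone (D.3.3) would lower the numbers further, but the plan gives no figure for it.

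**3. Children needed per group to end with 20.**
- At 84% recruitment alone: 20 / (0.84 × 0.80/150) = 4,465.
- At 84% recruitment and 10% dropout: 20 / (0.84 × 0.90 × 0.80/150) = 4,961.

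**4. The 2007 counts.** 8,528 + 3,065 = 11,593, or about 5,796 per group if split evenly.
- Diagnosed: 5,796 × 0.80/150 = 30.9.
- After 84% recruitment and 10% dropout: 30.9 × 0.84 × 0.90 = 23.4 (18.9 at 68%).

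**5. Precision.** The 95% half-width for a difference in means, in SD units and ignoring clinic clustering, is t(0.975, 2n − 2) × √(2/n):
- n = 20: 2.024 × 0.316 = 0.64
- n = 18: 2.032 × 0.333 = 0.68
- n = 16: 2.042 × 0.354 = 0.72

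Relative to 20 per group, the interval is about 6% wider at 18 and about 13% wider at 16.

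**The case against.** **D.5.3 may concern Aim 2 only.** A reader might infer that its statement about the adjusted sample size is simply false. The text does not support that. The section opens with the primary outcome, relies on CHICA's 1.3% field-omission rate, and uses the same dropout figure as the Aim 2 calculation, where the adjustment was made. It also speaks of compromised power, whereas Aim 3 is sized on estimation. The sentence is unlabelled in scope. That still needs correcting, because it stands under a heading for both aims.

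**The figure of 16 is not wholly the plan's own.** A reader might infer that the plan's rates give 16 per group. They do so only if Aim 2's dropout rate is carried over to Aim 3. The 84% is itself a past record rather than a forecast for this cohort. The figure of 18 enrolled needs only the 84%, and it is already below 20.

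**The 2007 counts may supply more children.** A reader might infer that 20 per group cannot be reached. That is not shown, since an even split of the 2007 counts gives about 23 after both losses. However, the plan calculates from 4000, not from those counts, and they include children under 18 months and possibly children already diagnosed.

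**The 4000 might already be net of refusal.** This does not stand. The 4000 is justified by clinic patient counts, and consent is sought only from the newly diagnosed.

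**The consequence is small.** This stands. All the projected numbers exceed 12. The plan states no half-width for Aim 3 and admits that it does not know how many newly diagnosed children there will be. The mixed model in D.5.2 also uses children with partial follow-up.

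**Conclusion.** The point holds and is minor. The Aim 3 projection of more than 20 per group is a count of diagnosed children (21.3), used as the size of a consented cohort followed for 12 months. On the plan's own 84% recruitment it is about 18 enrolled per group. If 10% dropout is assumed as well, about 16 have 12-month data, or about 13 at the parent network's 68%. These figures take 4000 per group as given and assume that every diagnosed child's family is contacted.

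The stated size is therefore overstated on its stated inputs, but the pilot is not undermined. The half-widths ignore clustering. With two clinics per arm they show only the relative loss from smaller numbers, not the precision that the trial will have.

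**What to change.** In D.4.1 (Aim 3), multiply the expected diagnoses by a recruitment rate and by a retention rate stated explicitly as an assumption for this cohort. Give two numbers per group, those expected to enrol and those expected to have 12-month data, and preferably the interval half-width at the latter.

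If the sponsor instead relies on the larger 2007 counts, replace 4000 with the figure used, show the calculation through to children with 12-month data, and say how children under 18 months and those already diagnosed were handled.

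In D.5.3, limit the statement about the adjusted sample size to Aim 2.

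The cost is protocol wording and possibly a less favourable stated figure. No patients need be added, since Aim 3 is a pilot sized on estimation.

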## **D.6 Future Work**

By the end of this study, we will have adapted CHICA for use in ASD screening, diagnosis and management and fully evaluated its capabilities in improving care in these areas. At that time, we will be uniquely positioned to study the CHICA ASD system in the “real” world, by focusing on widespread dissemination. Dissemination will be facilitated by the open source architecture of the CHICA system. This movement from the “laboratory” of our own clinics to eventual use worldwide is the true goal of translational research, and will complete the long road from development to clinical practice.
